Acupuncture can modulate autonomic nerve system activity [24], and central sympathetic activity is considered to influence hot flush activity [25]. Autonomic nerve system function is assessed by measuring heart rate variability [26]. Bone mass density is measured at baseline and after 12 months, to investigate rate of bone loss among women with climacteric symptoms. Evaluations further include measurements of serum FSH and estradiol at baseline and end of intervention, to confirm that the women are postmenopausal.

Participants are recruited to three centres (Tromsø, Oslo and Bergen), by the use of newspaper advertisements and promotion through media coverage. Informed consent is obtained from all participants before randomisation. See eligibility criteria in table 1.

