### Randomization

Participants are stratified by centre and thereafter block randomised (random block size) to additional acupuncture or no additional acupuncture. Staff at study headquarters at University Hospital of North Norway (UNN), which is not connected with the study, prepared the randomisation database and acts as a central randomisation service. Each local coordinator (Tromsø, Oslo and Bergen) obtains distance randomisation of included participants.

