### Statistical power and sample size

Calculations were made in consultation with a professional statistician. The sample size was calculated using NCSS (PASS 2002) programme, using data for hot flush frequency from many previous trials of HRT, herbs and acupuncture. With a baseline daily flush rate of 7.0 (SD 3.0), and assuming that the difference of interest is 20 percentage points (post-treatment flush rates of 3.5 and 4.9 for acupuncture and no acupuncture groups respectively, equivalent to reductions of 50% and 30%, and SD 3.5 for change in flush rate), and employing a two-sided, two-sample t-test for the changes, 100 women in each group were needed to identify a 20% difference with a power of 80% and α-value of 0.05. Assuming a total withdrawal and dropout rate of 30%, we estimated that a total sample size of 286 women is required.

Power calculations for the sub-study of biological variables are based on earlier studies of the CGRP excretion in urine during acupuncture treatment [15]. To identify a supposed 30% difference in CGRP urine excretion with a power of 80% and α-value of 0.05, we need 25–30 participants in each group. To allow for some measurement inaccuracies because CGRP and NYP are to be measured in early morning and evening urine samples, we will use 35 participants in each group.

Data entry is undertaken by the central coordinator, with checking of random 10% samples by the research fellow. Data on primary endpoint are entered by a person not connected to the study team, and who is blinded to treatment allocation.

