### Data analysis and handling

All analyses are conducted blinded to group allocation. Missing data are substituted by last value carried forward. The primary analysis is intention-to-treat, comparing mean changes from baseline to end of treatment after 12 weeks in the two groups, using a two-sample t-test. In the presence of meaningful baseline differences, analysis of covariance will be employed. It is anticipated that the data will be somewhat right-skewed, therefore analyses will be checked after appropriate data conversion, and also checked using non-parametric methods. Secondary analyses will compare the changes at different time points. Secondary measures will be analysed using appropriate parametric or non-parametric methods. Subgroup analyses include per-protocol analyses to assess efficacy of acupuncture care, and comparison of changes in hot flush rate among women grouped by TCM syndromes.

The trial headquarters is located at UNN Clinical Research Centre where they have experience in running multicenter studies. All data sheets are rendered anonymous by removing participant names and addresses. The personal information and the index that links trial numbers with individual participants is kept under lock and key in the possession of each local coordinator. Trial number alone identifies all computerised data. To prevent reporting bias, all the participant evaluation forms are administered by the trial headquarters in Tromsø. The participants return the evaluation forms to the trial headquarters in Tromsø.

Participants in either study group who choose to use any therapist-provided care to relieve hot flushes (e.g. massage, homeopathy or any prescribed medication to relieve hot flushes such as systemic estrogen or SSRI's from any source) during the 12 week study period, are followed up with registration of events and included in the intention-to-treat analysis.

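### The primary analysis is an unadjusted t-test on change with an undefined switch to ANCOVA; fixing ANCOVA on baseline and centre in advance would remove the data-dependent choice and may add precision

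*Protocol article*

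**What the plan says.** The Protocol article, Data analysis and handling, defines the primary intention-to-treat analysis as "comparing mean changes from baseline to end of treatment after 12 weeks in the two groups, using a two-sample t-test". The next sentence changes the method under a condition: "In the presence of meaningful baseline differences, analysis of covariance will be employed". It does not say which baseline variables count, how large a difference is meaningful, which covariates enter the model, or whether the t-test or the ANCOVA is primary once the condition is met. The same section says that analyses are done blind to allocation.

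The Randomization section states: "Participants are stratified by centre and thereafter block randomised (random block size) to additional acupuncture or no additional acupuncture". There are three centres. No analysis in the article names centre as a factor.

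Statistical power and sample size is built on the same unadjusted test of changes. It assumes a baseline mean of 7.0 with SD 3.0, "post-treatment flush rates of 3.5 and 4.9 for acupuncture and no acupuncture groups respectively", and "SD 3.5 for change in flush rate". It arrives at 100 women per group for 80% power at a two-sided 5% level, and 286 in total after 30% dropout. It gives neither the post-treatment SD nor the correlation between baseline and follow-up.

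**The concern.** Three things looked wrong.

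- **The method depends on the data.** Which of two tests yields the primary p-value is settled after looking at the baseline comparison, on a judgement with no written criterion. Two analysts applying the plan in good faith could report different primary results.
- **Baseline is used inefficiently.** Subtracting baseline amounts to fixing the slope of follow-up on baseline at 1. Women enter because their recorded flush count is high, so some regression to the mean is expected and the true slope may well be below 1. The change score then over-corrects: it has more variance than a baseline-adjusted estimate, and a chance baseline difference too small to trigger the switch carries into the treatment contrast.
- **The stratification factor is left out.** A two-sample t-test cannot use centre, so precision gained by stratifying does not reach the standard error.

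At stake are the precision of the main result and a single, unambiguous primary p-value.

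**Working it through.** **1. The plan's own figure.** Difference 4.9 − 3.5 = 1.4; SD of change 3.5; two-sided 5%. The normal formula gives 99 per group. With the noncentral t, power is 0.7997 at 99 and 0.8036 at 100 per group. 200/0.70 = 285.7, so 286. The stated size reproduces for the stated test.

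**2. Baseline adjustment.** Let s be the post-treatment SD (assumed). From Var(change) = 3.0² + s² − 2ρ(3.0)s = 3.5²:

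- ρ = (9 + s² − 12.25)/(6s)
- slope of follow-up on baseline = ρs/3.0
- ANCOVA residual SD = s√(1 − ρ²)

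For example, s = 3.0 gives ρ = 5.75/18 = 0.32 and residual SD 3.0 × √(1 − 0.102) = 2.84. The variance ratio is 2.84²/3.5² = 0.66.

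| Assumed s | ρ | Slope | Residual SD | Variance vs change score | Power, 100 per arm |
|---|---|---|---|---|---|
| 2.5 | 0.20 | 0.17 | 2.45 | 0.49 | 98% |
| 3.0 | 0.32 | 0.32 | 2.84 | 0.66 | 93% |
| 3.5 | 0.43 | 0.50 | 3.16 | 0.82 | 88% |
| 4.0 | 0.53 | 0.71 | 3.39 | 0.94 | 83% |
| 4.5 | 0.63 | 0.94 | 3.50 | 1.00 | 80% |

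Against 80% for the planned test, the gain runs from about 0 to 18 points. It vanishes where the slope is 1: 9 + s² − 12.25 = 18, so s = √21.25 = 4.6.

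**3. The conditional rule.** This was simulated with normal data, 100 per arm and 40,000 replicates per setting. Since no trigger is written, the assumed trigger is a baseline t-test at p < 0.05 or p < 0.20.

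| Assumed s | Type I error, rule followed (0.05 / 0.20 trigger) | Power, rule followed (0.05 / 0.20 trigger) | Type I error if the better test is reported |
|---|---|---|---|
| 2.5 | 3.4% / 2.6% | 82% / 87% | 8.3–8.5% |
| 3.0 | 4.0% / 3.2% | 82% / 85% | 7.5–7.8% |
| 3.5 | 4.4% / 4.1% | 81% / 83% | 6.9–7.1% |
| 4.0 | 4.8% / 4.7% | 81% / 81% | 6.1–6.2% |

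Followed mechanically, the rule is slightly conservative and recovers little of the gain in step 2.

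**4. Chance imbalance below the trigger.** The SE of the baseline difference at 100 per arm is 3.0 × √(2/100) = 0.42. A one-SE difference, which neither assumed trigger would catch, moves the change-score contrast by 0.42 × (1 − slope). That is 0.42 × 0.50 = 0.21 at s = 3.5 and 0.42 × 0.68 = 0.29 at s = 3.0, or 15% to 21% of the 1.4 target. It is part of the ordinary sampling error of the change score, not bias, and ANCOVA removes it.

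**5. Centre.** If centre explains an assumed share v of the change variance, the SD becomes 3.5√(1 − v). By the normal formula, power at 100 per arm goes from 80.7% to 81.5%, 82.7% and 84.6% for v = 2%, 5% and 10%, a gain of about 1 to 4 points.

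**The case against.** The defence has real substance.

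- **The stated test is valid.** A t-test on change is unbiased under randomisation; regression to the mean acts on both arms equally in expectation. The trial was sized for this test and keeps its 80% power. This stands, so a reader should not infer that the trial is underpowered or its estimate biased.
- **The SDs do not fix the correlation.** It is tempting to read 3.0 and 3.5 as implying a low baseline-to-follow-up correlation. They do not: without the post-treatment SD any row of the first table is possible, and at 4.5 the gain is gone. The two SDs are also drawn from many earlier trials and need not describe one population. This stands. Against it, an SD near 4.6 would be about 1.5 times the baseline SD (4.6/3.0) while the planned post-treatment means are 3.5 and 4.9, so a slope below 1 is plausible, though not established.
- **The switch need not inflate error.** Followed as a mechanical rule it is conservative. Inflation needs someone to choose the more favourable result, and blinding makes steering towards acupuncture harder. This stands in part: an imbalance between coded groups, or the smaller of two p-values, is visible without knowing which group is which.
- **The switch itself deals with imbalance.** It does so only above an unstated threshold; smaller differences stay unadjusted.
- **Centre matters little.** Leaving it out causes no bias and makes the test slightly conservative. The ANCOVA covariates are unlisted, so centre is not excluded there. This stands.
- **An analysis plan may supply the details.** Covariate lists and trigger definitions are often left to it. But the article itself states the unadjusted test and the conditional switch, so this is a rule badly fixed rather than detail omitted.

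**Conclusion.** The point holds as one of efficiency and of an unfixed primary method. The primary test is unadjusted, the move to ANCOVA rests on an undefined judgement made after seeing baseline data, and the stratification factor is in no stated analysis.

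The size depends on assumptions. The power forgone is about 0 to 18 points over post-treatment SDs of 4.5 down to 2.5, given the plan's SDs of 3.0 and 3.5, plus about 1 to 4 points for centre at 2 to 10% of variance explained. Type I error is about 3 to 5% if an assumed p-value trigger is applied mechanically. It is about 7 to 8% (post-treatment SDs of 3.0 to 3.5) if the better of the two tests could be reported; nothing in the article says that this is intended. The simulations assume normal data, whereas the article expects some right skew.

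A reader might infer that the planned test is invalid, that its error rate is necessarily inflated, or that omitting centre undermines the result. The article supports none of these. The change is worth making but is not a condition for a valid trial.

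**What to change.** Delete the conditional sentence. State one primary model: ANCOVA of the week-12 mean daily flush rate on treatment, with baseline flush rate and centre as prespecified covariates, used whatever the observed balance. Keep the unadjusted t-test on change as a named supportive analysis, and say that the ANCOVA estimate and p-value are the primary result.

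The cost is wording only. Baseline flush rate and centre are already recorded for every randomised woman. The sample size of 286 can stay: across the post-treatment SDs examined, the adjusted analysis has at least the planned power. The change should be fixed before any comparison of the groups is seen.

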**Methods/Design:**

The study is a multi-centre pragmatic randomised controlled trial with two parallel arms. Participants are postmenopausal women who document ≥7 flushes/24 hours and who are not using hormone replacement therapy or other medication that may influence flushes. According to power calculations 200 women are needed to detect a 50% reduction in flushes, and altogether 286 women will be recruited to allow for a 30% dropout rate.

The treatment group receives 10 sessions of Traditional Chinese Medicine acupuncture-care and self-care; the control group will engage in self-care only. A team of experienced Traditional Chinese Medicine acupuncturists give acupuncture treatments.

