**Discussion:**

The study tests acupuncture as a complete treatment package including the therapeutic relationship and expectation. The intervention period lasts for 12 weeks, with follow up at 6 and 12 months. Primary endpoint is change in daily hot flush frequency in the two groups from baseline to 12 weeks; secondary endpoint is health related quality of life, assessed by the Women's Health Questionnaire. We also collect data on Traditional Chinese Medicine diagnoses, and we examine treatment experiences using a qualitative approach. Finally we measure biological variables, to examine potential mechanisms for the effect of acupuncture. The study is funded by The Research Council of Norway.

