### Experimental intervention

Traditional acupuncturists, using diagnostic methods according to the principles of Traditional Chinese Medicine, diagnose TCM syndromes associated with the symptoms of menopausal hot flushes. The acupuncturists meet the criteria for membership in the Norwegian acupuncture society, "Norsk Akupunkturforening" (NAFO), and have at least five years experience of practice. There are four practitioners in Oslo, three in Bergen and three in Tromsø. This will ensure that the study tests the effects of TCM acupuncture-care, not the individual practitioner.

The Delphi technique [27] has been used to establish a consensus between acupuncturists regarding the standardized diagnostic criteria and treatment guidelines, as previously successfully used for acupuncture treatment of lateral epicondylitis [28].

After the initial diagnosis, each participant is treated with points selected according to the syndrome diagnosis. The acupuncturists are free to add individualised points to treat other symptoms related to the menopause (i.e. those included on the WHQ such as depression, anxiety, insomnia), but not unrelated symptoms. In addition, acupuncturists can use moxibustion (warmed needles) if indicated. The acupuncture treatment comprises up to 10 treatment sessions over 12 weeks. This period can be extended for 2 weeks to allow for personal circumstances. The minimum treatment defined 'per protocol' is 6 sessions.

The acupuncture-care group is free to use any over the counter (OTC) drugs and self-provided non-pharmaceutical intervention during the intervention period. In addition, they can use soy, specific dietary supplements and herbal medicines.

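### The one stated per-protocol rule can exclude only acupuncture women, so the analysis cannot by itself show efficacy; the TCM-syndrome comparison, as described, is only descriptive

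*Protocol article*

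**What the plan says.** In the protocol article, Data analysis and handling makes the intention-to-treat comparison of 12-week change primary. Two further analyses follow in the same paragraph: "Subgroup analyses include per-protocol analyses to assess efficacy of acupuncture care", and a "comparison of changes in hot flush rate among women grouped by TCM syndromes".

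The criterion for the first is under Experimental intervention: "The minimum treatment defined 'per protocol' is 6 sessions". No counterpart is given for the other arm, where the abstract says "the control group will engage in self-care only". Data analysis and handling also says "Participants in either study group who choose to use any therapist-provided care to relieve hot flushes" remain in the intention-to-treat analysis. It does not say whether they remain in the per-protocol set.

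On syndromes, Experimental intervention says the acupuncturists "diagnose TCM syndromes associated with the symptoms of menopausal hot flushes", and then: "After the initial diagnosis, each participant is treated with points selected according to the syndrome diagnosis". Neither Control intervention nor the baseline assessment listed under Effect measures mentions a TCM diagnosis. The abstract's Discussion says "We also collect data on Traditional Chinese Medicine diagnoses" and names no arm.

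**The concern.** Number of sessions is a post-randomisation variable that exists in one arm only. Under the stated rule, acupuncture women with fewer than 6 sessions leave the analysis, while control women who would have behaved the same way cannot be identified and stay. The two remaining groups may then differ in prognosis as well as treatment. The article nevertheless gives this analysis the task of assessing efficacy, so a difference produced by selection could be reported as a treatment effect.

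The syndrome comparison raises a related problem. If only treated women are diagnosed, the change within each syndrome mixes treatment response, natural course and regression to the mean. Regression to the mean is likely to matter here, because women qualify by documenting at least 7 flushes per 24 hours. Differences between syndromes would then say nothing about where acupuncture works better.

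**Working it through.** **The plan's own figure.** Statistical power and sample size gives a difference of 4.9 − 3.5 = 1.4 flushes/day, SD of change 3.5, two-sided α 0.05 and power 80%. The normal formula gives 99 per arm and the t-test version 99.08, which rounds up to the stated 100. Allowing for 30% dropout, 200/0.70 = 286, or 143 per arm. The plan's figures reproduce. It gives no figure for the per-protocol or syndrome analyses.

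**Size of a per-protocol bias.** Suppose there is no true effect. Let f be the share of the acupuncture arm with fewer than 6 sessions, and d how much less they improve than the rest of that arm. Both are assumptions, because the article gives neither. The arm mean is (1 − f)·m + f·(m − d) = m − f·d, where m is the mean of the retained women. Comparing retained women with all controls therefore gives a false contrast of f·d.

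With 143 per arm and f = 20%, 143 × 0.8 ≈ 114 women are retained. The SE is 3.5·√(1/114 + 1/143) ≈ 0.44. With d = 2 the contrast is 0.2 × 2 = 0.4, which is 0.4/0.44 ≈ 0.91 SE. The two-sided rejection probability is 1 − Φ(1.96 − 0.91) + Φ(−1.96 − 0.91) ≈ 0.149. The same steps give:

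| f | d (flushes/day) | False contrast | Share of 1.4 | Type I error, 143 per arm | Type I error, 100 per arm |
|---|---|---|---|---|---|
| 10% | 1 | 0.1 | 7% | 5.6% | 5.4% |
| 20% | 1 | 0.2 | 14% | 7.4% | 6.7% |
| 20% | 2 | 0.4 | 29% | 14.9% | 11.9% |
| 30% | 2 | 0.6 | 43% | 26.0% | 19.6% |

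The calculation keeps SD 3.5 in the retained set and uses the normal approximation. If d = 0 the contrast is zero. If d is negative (women stop because they improved), the same amounts count against acupuncture.

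**Is a gap near 2 far-fetched?** The plan carries the last value forward and expects 7.0 − 4.9 = 2.1 flushes/day of improvement with self-care. Suppose a woman leaves before the week-4 diary and her baseline value is carried forward. Her recorded change is zero, so she is 2.1 behind a woman who stayed, even if acupuncture adds nothing. If all of the expected 30% dropout were of this kind with fewer than 6 sessions, the false contrast would be 0.3 × 2.1 = 0.63 and the type I error about 28%. With half as many, it would be 0.15 × 2.1 ≈ 0.32 and about 11%. The first is an upper case, not a forecast.

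**Syndromes.** The text places the diagnosis at the first step of acupuncture treatment and nowhere in the control arm or the listed baseline assessment. Precision would also be limited. In an acupuncture arm of 100 to 143 women split equally (number of groups assumed), power to detect 1.4 between two syndromes is 52–66% with two groups and 37–49% with three. If both arms were diagnosed, an arm-by-syndrome interaction of 1.4 with two equal syndromes would have 29–39% power.

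**The case against.** The strongest reply is that the full per-protocol set is not shown. Analysis sets are commonly defined in the full protocol or SAP, and the remark about outside care in either group suggests that controls too might be excluded. A reader might infer that the analysis drops acupuncture women only and compares the rest with every control. The article does not say that, because it defines neither the comparator nor any control exclusions. This stands. It does not rescue the 6-session rule, which still acts on one arm and is still the only rule given.

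Second, the direction of bias is unknown. The number of sessions has a ceiling of 10 and no fixed total, so some women may stop because they are better. The larger figures also need a gap above the 1.4 target, and the mild case is close to the nominal 5%. This stands too: a bias in favour of acupuncture is conditional, not certain.

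Third, a reader might infer that the syndrome comparison has no controls and is intended to show a differential effect. The first part is a strong inference but not a stated fact: the abstract names no arm, and the data collection table and flow diagram are not in the text available. The second part is unsupported, since the article announces only a comparison of changes.

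Fourth, a complier-average estimate is not assumption-free. It assumes that fewer than 6 sessions have no effect. Methods/design describes a package that includes the therapeutic relationship and expectation, which may act from the first visit. Any such benefit would be credited to women with 6 or more sessions. This is a good reason to add the estimate alongside per-protocol and not to replace per-protocol with it.

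**Conclusion.** The point holds in a limited form. The only stated per-protocol criterion is applied after randomisation and can exclude women from the acupuncture arm only, so the analysis cannot by itself carry an efficacy reading. In the tabulated cases the false contrast runs from 0.1 flushes/day (type I error about 6%) to 0.6 (about 26%) with 143 per arm. All of these rest on assumed stopping shares and gaps, and on early stoppers doing worse. The sign reverses if they stopped because they improved, and there is no bias if stopping is unrelated to outcome.

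The syndrome comparison, as described, appears to be a within-arm comparison of change and can be read only descriptively. The documents do not support saying that it was planned as a test of effect modification.

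Both analyses are secondary. The primary intention-to-treat result, its error rate and the sample size do not change.

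**What to change.** 1. Keep the per-protocol analysis as supportive, and do not describe it as assessing efficacy. State its rules for both arms, including how women who use outside therapist care or prescribed drugs are handled.
2. Add a complier-average causal effect with randomisation as instrument, all randomised women included, and baseline flush rate and centre as covariates. Report it for at least 6 sessions and with number of sessions as dose. State the exclusion assumption and say that it is doubtful if 1–5 sessions, or the care package itself, help. The dose version relaxes the 6-session threshold but assumes a dose-response shape.
3. Label the TCM-syndrome comparison as descriptive, with no claim of differential effect unless controls are also diagnosed.

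The cost is analysis wording and one added estimate. Session counts should be recoverable, since Effect measures has the acupuncturists make a record at each session, though the article does not name the count as a variable. The added estimate is less precise. With 20% below 6 sessions and before covariate adjustment, its SE is about 3.5·√(2/143)/0.8 = 0.414/0.8 ≈ 0.52, against 0.44 for per-protocol. It also rests on an untestable assumption, which is why it should sit beside the intention-to-treat result and not in its place.
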